### 3.5. Study Phases and Assessments

Table 2 summarizes the type and frequency of safety and efficacy outcomes to be measured at each patient’s assessment by the investigators or designated site staff. 

Trial design with details on assessments per each phase are briefly outlined below:

#### 3.5.1. Screening Phase (Vscr, Emergency Department)

In Vscr, the site staff will assess eligibility according to the inclusion and exclusion criteria and obtain written informed consent. The informed consent and the whole study protocol is approved by the National Ethics Committee. Patients signing the informed consent will also explicitly consent to telephone calls by the investigators for follow-ups. A dated copy of the signed informed consent will be given to the patient. The enrolment of the participants will be considered valid once they have given their consent, completed the screening process and are deemed eligible. The moment of inclusion is defined as when the patient signs and dates the informed consent form. Any assessments and examinations related to the study are conducted after the informed consent has been obtained. Patients who sign the informed consent form also explicitly consent to telephone calls from the investigators for ongoing follow-ups.

At the ED, all patients are under continuous ECG monitoring. Once the signed informed consent has been obtained, all patients are fitted with a 24 h ECG holter monitoring device, without a removal of the ED ECG monitor. The flowchart of a patient’s baseline assessments is shown at Figure 1.

#### 3.5.2. Intervention Visit (V0)

The intervention visit is defined as the time at which the study staff intravenously administers the assigned drug and coincides with the screening visit. The drug that will be administered to each patient will be determined randomly, through a simple randomization process, as detailed in the relevant section. Patients in both groups will remain at the ED for a total of 6 h after starting the treatment, regardless of cardioversion status. If no adverse events occur during this time, including an AV block, sinus bradycardia < 50 bpm, syncope, presyncope, or systolic blood pressure < 90 mmHg and a cardioversion to sinus rhythm is successful, the patient will be discharged. Otherwise, the patient will be admitted to the hospital. Patients receiving flecainide with an unsuccessful cardioversion at 6 h will be hospitalized and receive amiodarone. Patients with an unsuccessful drug cardioversion after 24 h will undergo electrical cardioversion, according to the clinical judgment of the attending physician. All patients (i.e., those who were discharged at 6 h following a successful cardioversion and those who were hospitalized) will be under continuous 24 h ECG halter monitoring. The hospitalized patients will also be under continuous ECG monitoring until the time of a cardioversion. The 24 h ECG halter will be removed at 24 h from drug administration initiation, regardless of the cardioversion status.

In case of hemodynamic instability during or after the administration of the drug, or if the Δ (troponin at 1 h) is above the limit of the hospital’s laboratory troponin cut-off levels, the administration of the drug will cease, and the patient will be treated according to the guidelines. At discharge, the administration or non-administration of other medication will follow the guidelines, with the exception that patients will not receive treatment with a class Ic antiarrhythmic agent. 

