## 2. Objectives

The primary goals of this clinical trial are to prove the superiority of flecainide over amiodarone in the successful cardioversion of paroxysmal atrial fibrillation at the Emergency Department and to prove that the safety of flecainide is non-inferior to amiodarone in patients with coronary artery disease without residual ischemia and an ejection fraction over 35%. The secondary goals of the study are to prove the superiority of flecainide over amiodarone in the reduction in hospitalizations from the Emergency Department due to atrial fibrillation in the time taken to achieve cardioversion, and in the reduction in the need to conduct electrical cardioversion. A successful cardioversion is defined as the restoration of the sinus rhythm, documented by a 12 lead ECG lasting at least 1 h. 

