## 3. Materials and Methods

### 3.1. Trial Design Overview 

The FLECA-ED study [NCT05549752] is an ongoing, randomized, controlled, multi-center trial that aims to fill in the gaps relating to the use of flecainide for the cardioversion of AF in patients with a history of coronary artery disease without residual ischemia and a left ventricular ejection fraction > 35%. The trial’s start date was 24 March 2023, and the expected completion date is 1 November 2024. 

The trial population will be 200 consecutive all-comers to the emergency department with paroxysmal atrial fibrillation. These patients will be randomly assigned to the amiodarone or flecainide group, in a head-to-head comparison of the effectiveness and safety profile of the two drugs in this specific population. The study entails a baseline visit followed by the intervention visit (both at the ED), as well as one day follow-up at the investigation site for re-evaluation and a 30-day remote follow-up (phone visit). All eligible patients arriving at the ED that sign the informed consent and are enrolled in the trial will be fitted with a 24 h ECG halter device prior to drug administration in order to assess the incidence of PVCs, NSVT, SVT and bradycardia, as well as the time taken for cardioversion. For 6 h following the initiation of the drug administration, all the enrolled patients will stay at the Emergency Department under close monitoring. If the patient’s rhythm is not successfully restored to a sinus rhythm at 6 h, the patient will be admitted to the hospital and will receive intravenous amiodarone. 

This study will provide substantial data for the safety of flecainide in patients with coronary artery disease without residual ischemia. Furthermore, the direct comparison to amiodarone will demonstrate flecainide’s performance in terms of frequency and the time needed for successful cardioversion.

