### 3.6. Interventions

Individuals randomized to the flecainide arm will intravenously receive flecainide at a dose of 2.0 mg/kg (maximum dose of 150 mg) throughout the 10 min in the emergency department. Flecainide will be dissolved in a 100 mL D/W 5% solution.

Patients randomized to the amiodarone arm will intravenously receive amiodarone at a dose of 5.0–7.0 mg/kg over 1 h in the emergency department, as well as a follow-up dose of 50 mg/h (a maximum dose of 1000 mg) for up to 24 h (Figure 2). 

Intravenous metoprolol is administered in patients with atrial fibrillation exhibiting a ventricular rate over 100 bpm, according to a physician’s decision. 

Hemodynamically stable patients with an unsuccessful pharmacological cardioversion at 24 h will undergo electrical cardioversion, according to the clinical judgement of the treating physician.

Any prior use of an antiarrhythmic agent will be documented in the case report form (CRF) and all concomitant medications or other therapies will also be documented. For patients withdrawing from the study, the reasons and any follow-on therapy are to be documented in the CRF.

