### 3.7. Outcomes

The study’s primary endpoints are the frequencies of successful cardioversion within 6 h of drug administration as well as the combined frequency of PVCs, NSVT, SVT, bradycardia and hypotension during the same time frame. The main secondary endpoints are the frequency of patient discharges from the Emergency Department with a sinus rhythm and the frequency of successful cardioversion to a sinus rhythm within 24 h. All adverse effects, including extracardiac, will be assessed and categorized based on their severity, type and frequency. Table 3 lists all the study primary and secondary endpoints.

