**Secondary Outcomes**
The frequency of patient discharges from the Emergency Department in a sinus rhythm [Time Frame: From the drug initiation and for 6 h] The frequency of successful cardioversion to sinus rhythm [Time Frame: From the drug initiation and for 24 h, 24 h ECG Holter monitoring] The time until the cardioversion to sinus rhythm [Time Frame: From the drug initiation and for 6 h] The frequency of electrical cardioversion [Time Frame: From the drug initiation and for 24 h] The frequency of arrhythmias: burden of PVCs, NSVT episodes, SVT episodes [Time Frame: From the drug initiation and for 24 h] The frequency, severity and type of Adverse Events [Time Frame: From the drug initiation and for 30 days]

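### After 6 h the flecainide arm includes rescue with the comparator drug, so the 24-h and 30-day secondary endpoints compare treatment strategies and cannot support drug-versus-drug conclusions

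*Protocol article*

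**What the plan says.** Section 3.1 describes the trial as a randomised comparison of flecainide and amiodarone, "in a head-to-head comparison of the effectiveness and safety profile of the two drugs in this specific population". Section 2 lists superiority of flecainide "in the reduction in the need to conduct electrical cardioversion" among the secondary goals.

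For patients not in sinus rhythm at 6 h, Section 3.5.2 states: "Patients receiving flecainide with an unsuccessful cardioversion at 6 h will be hospitalized and receive amiodarone". Section 3.1 gives the rule without naming an arm: "the patient will be admitted to the hospital and will receive intravenous amiodarone". Under Section 3.6 the amiodarone arm has a one-hour loading infusion "as well as a follow-up dose of 50 mg/h (a maximum dose of 1000 mg) for up to 24 h". No different second drug is named for that arm.

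The first primary endpoint is the "frequencies of successful cardioversion within 6 h of drug administration", and the composite safety primary endpoint has the same window. Section 3.7 names "the frequency of successful cardioversion to a sinus rhythm within 24 h" as a main secondary endpoint. Table 3 repeats it as "The frequency of successful cardioversion to sinus rhythm [Time Frame: From the drug initiation and for 24 h, 24 h ECG Holter monitoring" and adds electrical cardioversion to 24 h, arrhythmia burden to 24 h and adverse events to 30 days.

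Section 3.8 analyses every endpoint by intention to treat. It explains this as analysis by the treatment given, disregarding compliance and changes of treatment, and adds per-protocol sensitivity analyses.

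**The concern.** The rescue drug for flecainide failures is the comparator itself. Up to 6 h the arms differ by drug. After 6 h one arm has had flecainide plus, in its failures, amiodarone, and the other has had amiodarone only. Because treatment changes are disregarded, everything that happens on rescue is counted in the flecainide arm.

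This acts in two directions. Conversions on rescue amiodarone raise that arm's 24-h cardioversion rate and may lower its need for electrical cardioversion, which would favour flecainide. Arrhythmias and adverse events after rescue are recorded against flecainide, although both drugs have by then been given. Neither result answers a question about flecainide as a drug, yet the protocol frames the comparison that way and attaches a superiority goal to electrical cardioversion.

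The per-protocol analysis does not separate the drugs, because a patient rescued at 6 h has followed the protocol.

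**Working it through.** **The plan's own figure.** The article gives no rate or power for any 24-h endpoint. Its one sample-size figure, 96 per arm (Section 3.4), is reproduced by a two-sided 5% test of 65% v 45% with pooled variance and 80% power (power at 96 per arm: 80.0%). It does not depend on the 24-h endpoints.

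**Which endpoints cross the 6-h switch (Table 3).**

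| Endpoint | Window | Affected by rescue |
|---|---|---|
| Cardioversion; composite safety endpoint (both primary) | 6 h | No |
| ED discharge in sinus rhythm; time to cardioversion | 6 h | No |
| Cardioversion | 24 h | Yes, raises the flecainide arm |
| Electrical cardioversion | 24 h | Yes, can lower the flecainide arm |
| Arrhythmia burden | 24 h | Yes, events on rescue count in the flecainide arm |
| Adverse events | 30 days | Yes, events on rescue count in the flecainide arm |

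**Formula.** Let p6 be the flecainide conversion rate at 6 h and r the share of its failures that convert on rescue between 6 and 24 h. With no other conversion after 6 h, the flecainide arm's 24-h rate is p6 + (1 − p6) × r, so rescue adds (1 − p6) × r. If some failures would have converted later without rescue, the net addition is smaller.

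**Inputs.** Section 3.4 gives 4-h rates of 65% (flecainide) and 23% (amiodarone). The 6-h and 24-h rates and r are assumptions.

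**Range over r, taking 65% as the 6-h rate** (35 of 100 rescued):

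| r | Added by rescue | Flecainide arm at 24 h |
|---|---|---|
| 10% | 3.5 points | 68.5% |
| 23% | 8.1 points | 73.1% |
| 40% | 14.0 points | 79.0% |
| 60% | 21.0 points | 86.0% |

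Against an assumed 60% in the amiodarone arm, flecainide alone differs by +5 points; r of 23%, 40% and 60% turns this into +13, +19 and +26. Against an assumed 70%, −5 becomes +3, +9 and +16, so the sign can change.

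**Three constant-hazard scenarios**, with amiodarone converting at the same hazard as rescue and as assigned drug:

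- A. Both 4-h rates extrapolated. Flecainide at 6 h: 1 − 0.35^1.5 = 79.3% (about 21 of 100 rescued). Amiodarone at 24 h: 1 − 0.77^6 = 79.2%. r = 1 − 0.77^4.5 = 69.2%. Flecainide arm: 0.793 + 0.207 × 0.692 = 93.6%.
- B. 65% and 23% taken as 6-h rates. Amiodarone at 24 h: 1 − 0.77^4 = 64.8%. r = 1 − 0.77^3 = 54.3%. Flecainide arm: 0.65 + 0.35 × 0.543 = 84.0%.
- C. Flecainide 65% at 6 h, amiodarone hazard as in A. Flecainide arm: 0.65 + 0.35 × 0.692 = 89.2% v 79.2%.

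| Scenario | Difference without rescue | Difference as analysed | Added by rescue | Power at 100 per arm, as analysed |
|---|---|---|---|---|
| A | +0.1 | +14.5 | 14.3 | 85% |
| B | +0.2 | +19.2 | 19.0 | 88% |
| C | −14.2 | +10.0 | 24.2 | 49% |

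The near-ties without rescue in A and B come from the chosen hazards. The direction does not: any extra conversion on rescue raises the flecainide arm.

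**The case against.** **The head-to-head question is mostly protected.** Both primary endpoints and two secondary endpoints stop at 6 h, before rescue. Section 2 attaches no explicit superiority goal to 24-h cardioversion. The same paragraph of Section 3.1 that announces the head-to-head comparison also discloses amiodarone after 6 h. All of this stands and limits the point. What remains is that the head-to-head description covers the whole trial without excepting the later endpoints, and that Section 2 does claim superiority for electrical cardioversion, whose window extends beyond the switch.

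**The randomised comparison is valid.** This also stands. Comparing a flecainide-first strategy with amiodarone by randomised arm is legitimate. Only its reading as a drug effect fails.

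**A reader might infer that a significant 24-h result would be produced wholly by amiodarone, with 85% to 88% probability.** The documents do not support this. Those figures belong to scenarios A and B; scenario C, equally compatible with the article, gives 49%.

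**A reader might infer that rescue is credited to flecainide at 30 days too.** It is not. The only 30-day endpoint is adverse events, where rescue counts against flecainide.

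**A reader might infer that the plan leaves open where rescued patients are counted.** Defining intention to treat by the treatment given is wrong wording, but the rest of that sentence disregards treatment changes, which points to the initial group.

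**Counting rescue as failure would seem to isolate the drug.** It would not. Every flecainide failure is due rescue at 6 h, so this fixes flecainide at its 6-h rate while amiodarone has 18 more hours. In scenario C that is 65% v 79.2%, an asymmetry in favour of amiodarone.

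**These are details for the analysis plan.** Table layouts are. The mismatch between the announced comparison and the one that the design delivers is in the article itself.

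**Conclusion.** The concern holds for the interpretation of the four secondary endpoints that run past 6 h. They compare flecainide followed by amiodarone on failure with amiodarone alone. They cannot support a drug-level head-to-head conclusion, or superiority in reducing electrical cardioversion as an effect of flecainide.

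The direction for 24-h cardioversion follows from the design; the size cannot be computed from the documents. With assumed 6-h flecainide rates of 65% to 79%, about 21 to 35 of 100 patients would be rescued. The 24-h difference could shift by several to about 20 points, and by 24 in the most extreme of the three scenarios. These figures assume no conversion after 6 h other than on rescue.

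For electrical cardioversion there is a further uncertainty. Sections 3.5.2 and 3.6 place it after drug failure at 24 h, while its Table 3 window ends at 24 h. These passages must be reconciled before one can say how many procedures the endpoint captures.

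The 6-h endpoints, including both primary endpoints, and the sample size are not touched.

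**What to change.** - Keep the analysis by randomised arm. In Section 3.8, define intention to treat by randomised assignment instead of by treatment given.
- State that all comparisons beyond 6 h, including electrical cardioversion, compare treatment strategies. Reword the Section 2 goal on electrical cardioversion and the head-to-head statement in Section 3.1 to match.
- Restrict drug-versus-drug conclusions to the 6-h endpoints.
- Report 24-h arrhythmias and 30-day adverse events separately before and after the start of rescue amiodarone. The later part concerns patients selected by failure at 6 h and should be read descriptively.
- If an analysis counting rescue as failure is added, make it supportive only, with the caveat that it holds flecainide at its 6-h rate and so favours amiodarone.

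The cost is some wording, a small amount of extra analysis and a less favourable 24-h claim for flecainide. Section 3.6 says that concomitant medication is documented but does not mention start times, so the sponsor should confirm that the start time of rescue is recorded. No clinical rule, visit or sample size changes.

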### 3.3. Randomization

Randomization is performed via an eCRF platform developed by PHARMASSIST CRO (Athens, Greece), which is also used to document all the study contacts, assessments and outcomes. 

Patients and researchers are aware of the treatment group that patients have been randomized to. The two antiarrhythmic drugs, amiodarone and flecainide, have different dosages and a different time and method of administration, making the design of a single or double-blinded trial design difficult in an Emergency Department setting. 

The process of active randomization in each of the two groups in a 1:1 ratio contributes to the prevention of selection bias and is undertaken by an independent authorized researcher who is not taking part in the rest of the trial’s procedures.

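### The goal is less need for electrical cardioversion, but the endpoint counts procedures within 24 h while the protocol places them at or after 24 h, at physician discretion in an open-label trial

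*Protocol article*

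**What the plan says.** - **Goal (Section 2, Objectives).** One secondary goal is superiority "in the reduction in the need to conduct electrical cardioversion". The same section defines successful cardioversion as sinus rhythm, documented on a 12-lead ECG, that lasts at least 1 h.
- **Endpoint (Table 3, Secondary Outcomes).** "The frequency of electrical cardioversion [Time Frame: From the drug initiation and for 24 h". This is a count of procedures. No scoring is stated for a patient who remains in AF and has no procedure.
- **Trigger, Section 3.5.2.** "Patients with an unsuccessful drug cardioversion after 24 h will undergo electrical cardioversion, according to the clinical judgment of the attending physician".
- **Trigger, Section 3.6.** "Hemodynamically stable patients with an unsuccessful pharmacological cardioversion at 24 h will undergo electrical cardioversion, according to the clinical judgement of the treating physician".
- **Blinding (Section 3.3).** "Patients and researchers are aware of the treatment group that patients have been randomized to".
- **Treatment before the decision (Section 3.5.2).** "Patients receiving flecainide with an unsuccessful cardioversion at 6 h will be hospitalized and receive amiodarone". Under Section 3.6, the amiodarone arm continues its infusion for up to 24 h.
- **Rhythm endpoint (Table 3).** Successful cardioversion by 24 h is a separate secondary endpoint, with "Time Frame: From the drug initiation and for 24 h, 24 h ECG Holter monitoring".

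**The concern.** Need and performance are different quantities. A patient whom the drug has failed needs a further attempt at conversion, whether or not anyone carries it out. The endpoint records only whether it was carried out, and so gives the favourable score both to a patient who converted and to one left in AF.

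Two features of the plan make this matter. First, the counting window closes at 24 h, whereas the procedure that follows drug failure is placed at or after 24 h. The patients who define need may therefore hardly enter the count. Second, the decision rests on clinical judgement without stated criteria, in a trial where the arm is known. Repairing the window alone would leave a count that depends partly on physician behaviour. At stake is whether one of the stated secondary goals can be read as a drug effect.

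**Working it through.** **No planned figure to reproduce.** The document gives no expected rate, effect size or power for electrical cardioversion. The stated 96 per arm concerns the primary efficacy endpoint and has no bearing here.

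**Step 1: the endpoint as written.**

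| Item | Place | Timing |
|---|---|---|
| Counting window | Table 3 | drug initiation to 24 h |
| Procedure after drug failure | Section 3.5.2 | after 24 h |
| Procedure after drug failure | Section 3.6 | at 24 h |

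Under Section 3.5.2 the procedure falls outside the window; under Section 3.6 it falls on its edge. Read literally, the count captures mainly procedures done earlier for other reasons, and most patients still in AF at 24 h score zero. Patients who converted also score zero.

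**Step 2: the endpoint if the window is extended.** Suppose every procedure given for drug failure is counted. Then in each arm

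procedure rate = (proportion not converted by drug) × (proportion of those who receive the procedure).

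Only the first factor is drug effect. The second is a discretionary decision made with the arm known.

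**Step 3: illustration.** All rates below are assumptions; none is in the document. There are 100 patients per arm (the recruitment target in Section 3.4). The test is the pooled z test of two proportions at two-sided 0.05:

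z = (p1 − p2) / √[2·p̄(1 − p̄)/100], with p̄ = (p1 + p2)/2.

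Rejection probabilities come from exact enumeration of the two binomial distributions. Drug failure is identical in the two arms, so any rejection is false.

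| Failure, both arms | Share of failures treated | Procedure rates | Probability of significance |
|---|---|---|---|
| 10% | 90% v 70% | 0.10 × 0.90 = 9% v 0.10 × 0.70 = 7% | about 8% |
| 20% | 90% v 60% | 0.20 × 0.90 = 18% v 0.20 × 0.60 = 12% | about 22% |
| 30% | 90% v 50% | 0.30 × 0.90 = 27% v 0.30 × 0.50 = 15% | about 56% |

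With equal practice in the two arms the figure is about 5%.

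**Step 4: masking.** A true halving of drug failure, 10% v 20%, vanishes if 90% v 45% of failures receive the procedure: 0.10 × 0.90 = 0.20 × 0.45 = 9% in both arms.

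Steps 3 and 4 describe the extended-window endpoint, not the one now in Table 3.

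**The case against.** **The protocol makes the procedure the default.** Both sections say that patients will undergo it. That is fair, but both attach physician judgement in the same sentence and give no criteria. How many failures would go untreated cannot be told from the text.

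**The differential is assumed.** This stands. A reader might infer from the table above that the endpoint is biased by a known amount or towards a known arm. The document does not support that: it gives no procedure rates and no reason for a gap of any given size or direction. The mildest scenario moves the error rate only from 5% to about 8%.

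**Two drugs against one.** A reader might infer that physicians would treat the arms differently because flecainide failures have had two drugs by 24 h and amiodarone failures one. This is a weak mechanism. Sections 3.1, 3.5.2 and 3.6 together put non-converters in both arms on intravenous amiodarone after 6 h. Section 3.3 also speaks of patients and researchers being unblinded and does not name the attending physician, although nothing in the text shields that physician from the allocation.

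**Remaining AF is already visible.** Conversion by 24 h on Holter is its own endpoint, and Section 3.7 names it among the main secondary endpoints; electrical cardioversion is not named there. A patient left in AF is a failure on that endpoint, which limits the harm to the trial as a whole. It does not change how the patient scores on the endpoint that directly serves the goal of reduced need.

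**Counting procedures is a common pragmatic choice, and criteria may sit in the full protocol.** Criteria may well be there. But the article itself states the goal, the endpoint, its window and the timing of the procedure, and these do not fit together.

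**Conclusion.** The point holds as a mismatch between stated texts. The goal is need; the endpoint is procedures performed within 24 h; the procedure that follows drug failure is placed at or after 24 h. As written, most patients still in AF at 24 h score the same as patients who converted. Extending the window would cure the timing but leave a count that blends drug failure with discretionary, unblinded decisions.

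The size of any resulting bias is unknown. The range of about 8% to 56% rests on three assumptions: all procedures for drug failure are counted, failure is equal in the two arms, and readiness to perform the procedure differs by arm. It shows what could happen, not what will.

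The consequence is limited to one secondary endpoint. Both primary endpoints are unaffected.

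**What to change.** 1. Reconcile Section 3.5.2, Section 3.6 and Table 3 on when electrical cardioversion takes place relative to the 24 h window. Which timing is clinically right is for the investigators.
2. Analyse need as: electrical cardioversion performed within 24 h, or no drug-induced sinus rhythm lasting at least 1 h (the Section 2 definition) by 24 h. Score it from the Holter and the 24 h ECG, preferably read blind to arm.
3. State that a relapse after a valid 1 h conversion does not count as need unless electrical cardioversion is given. Scoring simply on rhythm at the 24 h visit would turn a success under Section 2 into a failure here.
4. State how a conversion that begins in the last hour is scored, since the Holter comes off at 24 h.
5. Report procedures actually delivered descriptively, beside 24 h rhythm status, over a window that includes them.

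**Cost.** A change of endpoint wording, plus blinded reading if adopted. The recordings are already collected, and clinical care is unchanged. The downside is that the redefined endpoint overlaps heavily with the existing 24 h conversion endpoint and adds less separate information.
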